## Abstract

**Background:**

Low back pain is a global public health problem and a leading cause of disability all over the world. The lifetime prevalence of low back pain is 70–80% and a significant proportion of people affected develop chronic low back pain (CLBP). Besides a severe negative impact on people’s health and health-related quality of life, CLBP is associated with substantial costs for society. Medical costs for the management of CLBP and costs for production losses due to absenteeism from work are sizeable. Pharmaceuticals, physical activity, manipulation, and multidisciplinary rehabilitation interventions are examples of widely used treatments for CLBP. However, the scientific basis to recommend the use of one treatment over another is limited and more research is needed to study the effects, costs and cost-effectiveness of treatments for CLBP in clinical practice.

The aim of the study is to evaluate the effectiveness (back pain-related functional limitation, back pain intensity, general health, health-related quality of life, and working status), costs (medical costs and costs for production losses) and cost-effectiveness of chiropractic care and physiotherapy when added to information and advice in the treatment of patients with non-specific CLBP in Sweden.

**Methods/design:**

This is a pragmatic randomised controlled trial, where participants are recruited through six primary care rehabilitation units (PCRUs) in Stockholm County Council, Sweden. Individuals with non-specific CLBP are individually randomised to one of four treatment groups: ‘information and advice’; ‘physiotherapy, and information and advice’; ‘chiropractic care, and information and advice’; or ‘chiropractic care, physiotherapy, and information and advice’. A sample size of 600 participants will be recruited during a period of 33 months. A computer-based questionnaire is used to collect data on back pain-related functional limitation (Oswestry Disability Index), pain intensity (Numeric Rating Scale), general health (self-rated health), health-related quality of life (EQ-5D-3L), and working status (measured as percentage of full-time work). Data will be collected at baseline, and at 3, 6, and 12 months after baseline.

**Discussion:**

The results from our study should be considered when producing evidence-based guidelines and recommendations on which treatment strategies to use for CLBP.

**Trial registration:**

ISRCTN registry, ID: ISRCTN15830360. Registered prospectively on 2 February 2017.

**Electronic supplementary material:**

The online version of this article (doi:10.1186/s13063-017-2351-3) contains supplementary material, which is available to authorized users.

## Background

Low back pain is one of the leading causes of disability across the world [1]. In the World Health Organisation (WHO) study on the global burden of disease, low back pain accounted for close to 11% of the total number of years lived in disability (YLD), making low back pain the leading cause of YLD in the world [1]. The total cost of low back pain to society was estimated at €1 860 million in Sweden in 2001 [2]. The indirect costs due to lost productivity were sizeable and accounted for 84% of the total cost [2]. In Sweden, low back pain is the most common reason for granting sick leave for patients with musculoskeletal disorders [3]. The lifetime prevalence of low back pain is 70–80% and a significant proportion of patients (10–20%) develop chronic low back pain (CLBP) lasting for at least 3 months [4, 5]. CLBP is associated with long-term pain, impaired function, and a severe negative impact on people’s health and health-related quality of life (HRQoL) [5]. In addition, CLBP is associated with substantial costs arising from within, but also outside, the health care sector. It is estimated that the total yearly cost for a patient with CLBP is SEK 227,000 within primary care [6, 7]. The indirect costs for production losses due to lost work days stood for about 85% of the total costs [6]. Health care systems should prioritise identifying effective and cost-effective treatment strategies to decrease the disease burden of CLBP.

A wide range of treatment options exist in the treatment and management of CLBP. Different pharmacological and non-pharmacological treatments, like physical activity, manipulation, and multidisciplinary rehabilitation interventions, are widely used alone or in combination [8, 9]. According to a survey published in a report by the Swedish Agency for Health Technology Assessment and Assessment of Social Services (SBU) [7], treatments for acute back pain in Sweden are often given by physiotherapists, chiropractors or naprapaths. While all of these occupational groups provide information and advice to stay active, they usually combine different interventions [7]. Physiotherapists typically also use different types of training and exercise in the treatment of acute back pain, than those used by chiropractors. For example, in the survey by SBU [7], 69% of the physiotherapists stated that they frequently used ‘circulation training’ as compared to 36% of chiropractors [7]. Chiropractors and naprapaths also use forms of manual therapies that physiotherapists do not, in general, use. The results in the survey showed that 13% of the physiotherapists regularly used spinal manipulation whereas the corresponding figure for chiropractors was 96% [7]. The report by SBU (2016) probably also reflects what occupational groups and treatments are involved in the treatment of patients with CLBP [7]. Our study will further increase the knowledge on what treatments physiotherapists and chiropractors currently use for the treatment of CLBP in Sweden.

The scientific basis to recommend the use of one treatment alternative over another is inadequate or limited and, therefore, more research is needed to study the effectiveness [9–11], and cost-effectiveness [12–15] of treatments for CLBP. According to findings in systematic literature reviews, there is high-quality evidence that spinal manipulation is as effective as other therapies (exercise therapy, standard medical care or physiotherapy) in reducing pain and improving function [10]. Furthermore, there is low-to-moderate evidence for (motor control) exercise to be clinically important, when compared to minimal intervention, and there is moderate-to-good evidence that motor control exercises have similar outcomes as other exercises and manual therapies [11]. There is moderate evidence that multidisciplinary treatments are more likely to have less pain and disability for patients compared to patients receiving usual care or physiotherapy [9]. However, SBU (2015) stated in a comment that the results in Kamper et al. (2015) were uncertain and maybe due to publication bias [9, 16].

In a previous pragmatic randomised controlled trial (RCT) in Sweden, Skargren et al. [12] compared the outcomes and costs of chiropractic care and physiotherapy as a primary treatment for patients with back and neck pain over a 1-year follow-up [14]. No difference in costs and outcomes were demonstrated for the total population. However, subgroup analyses showed that patients with acute, uncomplicated back pain gained more from chiropractic care at a similar cost, whereas patients with chronic back pain gained more from physiotherapy with a slightly reduced cost [12]. Niemisto et al. (2003) found that a combined intervention (advice, physiotherapy, and spinal manipulation) was more effective in reducing pain and disability than a physician consultation alone [13]. There were no significant differences in costs between the treatment groups [13]. In a follow-up study 2 years later, it was indicated that a physician consultation was cost-effective [14]. A cost-effectiveness study conducted alongside a RCT, concluded that spinal manipulation was a cost-effective addition to ‘best care’ for back pain in general practice, but also found that manipulation alone probably was cost-effective compared with manipulation followed by exercise in a UK setting [15].

With limited health care resources and stretched health care budgets, it is important to strive for efficient use of scarce resources [17]. Economic evaluation is a method for assessing costs and effectiveness of alternative ways of allocating resources to assist decisions aimed at improving efficiency [17, 18]. It also constitutes an important input for guiding clinical decisions. To be useful for decision-makers as an input to improve decision-making on the societal efficiency of the allocation of health care resources, it is important that the economic evaluation is based on a societal perspective, including costs both within (e.g. costs for pharmaceuticals, and costs for hospital and ambulatory care) and outside (e.g. indirect costs for decreased labour production) the health care system [18, 19]. In economic evaluations it is common to carry out cost-effectiveness analyses, where costs are measured in monetary terms and effectiveness in non-monetary terms. In this type of analysis, where the aim is to maximise the health gains for a specific cost constraint, it is crucial to use an outcome measure that combines effects on quality and quantity of life into one measure. The most commonly used measure of this sort is the quality-adjusted life year (QALY) [17]. This type of outcome measure is also recommended by, e.g. the National Institute for Health and Care Excellence (NICE) in England and Wales, and by the Dental and Pharmaceutical Benefits Agency in Sweden [20, 21].

Economic evaluation can be used to guide resource allocation decisions on which (if any) treatments for CLBP should be recommended. To achieve valid and reliable cost-effectiveness results in the area of CLBP the economic evaluation should be conducted alongside a RCT designed to reflect the clinical situation to which the decision is being applied and with a sufficient follow-up period carried out in well-defined study populations [22, 23]. This opens up the possibility to perform the economic evaluation based on data characterised by both high internal and external validity. A limitation of conducting an economic evaluation alongside a RCT is that the sample size is usually determined based on primary clinical endpoints in the trial. This implies that the power to detect different hypothesised cost-effectiveness results may be low. However, by using the net benefit approach, it is possible to investigate the power in a cost-effectiveness study that is implied by the given sample size in the RCT [24]. An advantage of using a so-called pragmatic RCT as a basis for the economic evaluation is that patient-level trial data provide an unbiased estimate of the effectiveness of interventions as reflected in clinical practice [23]. In addition, the RCT provides an opportunity for collecting data on the resources used to estimate costs and cost-effectiveness [19].

Currently, there are no clinical guidelines in Sweden on which treatment option should be used for CLBP [25]. This reflects a lack of knowledge on the effectiveness and cost-effectiveness of different treatment strategies for CLBP in a Swedish context [25, 26]. Thus, it is important to increase this knowledge. This is central for government agencies and county councils to be able to produce evidence-based guidelines and recommendations on which treatment strategies to use for CLBP.

In Sweden, patients with low back pain are often treated by either chiropractors or physiotherapists. Sometimes patients are treated by chiropractors and physiotherapists in collaboration. Besides providing general information and advice, these occupational groups usually recommend exercise (mostly recommended by physiotherapists) and manual therapies (mostly recommended by chiropractors) [7]. These treatment alternatives are also recommended in guidelines in different parts of the world [27]. As noted above, although a wide range of treatments exist for CLBP, the scientific basis to recommend the use of one treatment alternative over another is limited. There is, therefore, a need for well-designed clinical trials investigating both the effectiveness and cost-effectiveness of treatments for CLBP. Cost-effectiveness studies may provide valuable information on whether it is good value for money to use treatments and examinations provided by chiropractors and/or physiotherapists, in addition to only providing information and advice. Information both about the cost-effectiveness and effectiveness of treatments for CLBP is crucial for decisions aiming at improving the efficiency in the allocation of limited resources for the treatment of CLBP. The results from our study will improve the basis for health care decision-making and policy recommendations and should be considered when producing and updating evidence-based guidelines and recommendations on which treatment strategies to use for CLBP.

The aim of the study is to evaluate the effectiveness (back pain-related functional limitation, back pain intensity, general health, HRQoL, and working status), costs (medical costs and costs for production losses) and cost-effectiveness of chiropractic care and physiotherapy when added to information and advice in the treatment of patients with non-specific CLBP in Sweden.

Research questions:How do chiropractic care and physiotherapy, chiropractic care, or physiotherapy, when added to information and advice, impact outcomes (back pain-related functional limitation, back pain intensity, general health, HRQoL, and working status) as compared with only information and advice?Which (if any) of chiropractic care and physiotherapy, chiropractic care, or physiotherapy, when added to information and advice, is a cost-effective treatment strategy when compared to each other, and when compared with only information and advice?

## Methods/design

### Design

This is a multicentre, pragmatic RCT, approved by the Regional Ethical Review Board, Stockholm (Dnr: 2016/1318-31-31), and prospectively registered in the ISRCTN Registry (2017-02-20: ISRCTN15830360). The reasons for a pragmatic design are to reflect clinical practice and to limit per-protocol effects on the outcomes [23]. Each participant’s treatment is at the discretion of the individual chiropractor and/or physiotherapist. In Sweden, there are no official guidelines that define what those treatments typically include or how many sessions are standard. This study protocol has followed the Standard Protocol Items: Recommendations for Interventional Trials (SPIRIT) Guidelines (Additional file 1). The trial will be conducted and reported according to the reporting of pragmatic trials: an extension of the Consolidated Standards of Reporting Trials (CONSORT) Statement [28].

### Setting

The study will be conducted at six primary care rehabilitation units (PCRUs) in Stockholm County Council, Sweden. If needed, additional units will be included. The operations manager for each PCRU has signed a written certificate to assure that they will provide sufficient resources to both carry out the study and guarantee the safety of the participants. The PCRUs are reimbursed through the Stockholm County Council. Twelve PCRUs in the Stockholm County Council were initially informed about the study by email and invited to participate. For each of the six PCRUs interested in participating, an information meeting was scheduled. Before the start of the study each PCRU was informed about the study methods in more detail and given the opportunity to give feedback on how to improve the efficiency in the recruitment of participants.

### Characteristics of participants

The study includes individuals aged between 18 to 60 years, who are willing to participate in any of the included treatment groups (‘information and advice’; ‘physiotherapy, and information and advice’; ‘chiropractic care, and information and advice’; or ‘chiropractic care, physiotherapy, and information and advice’). All patients give written informed consent. The inclusion and exclusion of study participants is done to mimic the clinical praxis of Swedish primary health care, where the first patient contact usually takes place by phone. Inclusion criteria are: pain located below the costal margin and above the inferior gluteal folds, reoccurring low back pain for at least 3 months, age between 18 to 60 years, can stand or walk independently, and being Swedish speaking and literate. Exclusion criteria are: pain attributable to a known specific pathology (e.g. pain related to tumours, fractures, or fibromyalgia), lack of written informed consent, pregnancy or less than 6 months postpartum or post weaning, been treated for low back pain by a chiropractor and/or physiotherapist in the previous 1 month.

### Recruitment procedures

All participants are recruited through the PCRUs. Individuals with low back pain who contact the PCRU by phone are informed about the study and invited to participate. For individuals who are willing to participate (orally informed consent is given), and who meet the eligibility criteria (assessed by a primary health care staff member), a first (baseline) visit is scheduled at the PCRU. Information about the study will also be sent by email to the participants, after the phone contact and before the first PCRU visit. During the first visit to the PCRU, the participants sign a letter of informed consent before the treatment starts. At each PCRU two study coordinators (chiropractor and physiotherapist) are responsible for the enrolment of participants. Being a pragmatic RCT, there are no criteria for discontinuing or modifying allocated interventions, or improving adherence for a given trial participant. There is also no relevant concomitant care or intervention permitted or prohibited during the trial. The patients have the option to withdraw from the study at any point in time.

The recruitment of participants needs to be carefully monitored for each PCRU without any interaction between researchers and potential study participants. Throughout the study, the study coordinators at each PCRU will be contacted by the first author (FG) on a weekly basis about the enrolment of participants and the recruitment rate. During the start of the study (first 4 weeks) FG also assesses whether the information made available to each PCRU is clear regarding study methods and recruitment procedures. If needed, the information about study methods and recruitment procedures will be updated and clarified. After potential amendments, all PCRUs will continue the recruitment of participants according to the updated procedures. Additionally, FG will meet all the study coordinators on a monthly basis to review and gain feedback on the enrolment procedures and the recruitment rate.

### Randomisation

Each PCRU will continue to include subjects until the required total number of subjects (*n* = 600) is achieved (Fig. 1). All patients who give informed consent and who fulfil the eligibility criteria will be randomised. Participants are randomised to one of four treatments: ‘information and advice’; ‘physiotherapy, and information and advice’; ‘chiropractic care, and information and advice’; or ‘chiropractic care, physiotherapy, and information and advice’. A computer-generated, block randomisation list is produced to allocate participants to the treatment wings. The randomisation list and the allocation sequence are generated by a statistician who is not involved in the study. The sequence is concealed from the researchers involved in enrolling and assessing participants by using sequentially numbered, opaque, sealed envelopes. All researchers involved in the study will be blinded to block size(s) and randomisation list. Thus, the researchers do not know the block size(s) or if there is only one block size or different block sizes. This information (about block size(s) and randomisation list) is only known by the independent statistician who is not involved in the trial. The randomisation list will be in the possession of the statistician for the duration of the study. Envelopes will only be opened when it is time to allocate the intervention. The primary health care staff member opens the envelope during the phone call (but does not reveal the allocation to the participant), and schedules a time for the first visit. During the first visit at the PCRU, the health care provider (chiropractor and/or physiotherapist) will reveal which treatment group the participant has been randomised to.

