### Data collection

Data will be collected at baseline (after randomisation and before the treatment starts), and at follow-up, 3, 6, and 12 months after baseline. Each participant fills out a computer-based questionnaire at each measurement occasion. The day before each follow-up occasion, each participant is sent a reminder by email to fill out the questionnaire. If needed, a second and a third reminder is sent 2 and 7 days after the follow-up occasion. All data will be obtained from the computer-based questionnaire and from the chiropractor and/or physiotherapist reporting the number and content of treatments.

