#### Baseline

Baseline data will be collected during the first visit or at 1–4 days before the first visit at the PCRU. Data on individual characteristics (age, sex, education, smoking status, physical activity, use of pain killers, and pain duration), outcome measures (back pain-related functional limitation, pain intensity, general health, HRQoL, working status) and resource consumption (pharmaceuticals, health care visits, clinical examinations, and hospital days) are collected.

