### Statistical analysis

The main analysis will be conducted as an intention-to-treat (ITT) analysis for all participants that are included in the study [50]. Pattern of missing data and dropout will be examined and if appropriate multiple imputations will be used based on the nature of the missing data. The primary analysis is to evaluate between group differences in change on ODI scores at 6 months. All statistical tests are carried out at the 5% significance level (two-sided).

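### Baseline ODI can be answered after the allocation is revealed, and the ITT wording does not secure patients lost between envelope opening and written consent

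*Protocol article*

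**What the plan says.** All references are to the protocol article.

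- **Phone call.** Recruitment procedures puts oral consent and the eligibility check at the phone contact: "For individuals who are willing to participate (orally informed consent is given), and who meet the eligibility criteria (assessed by a primary health care staff". Randomisation adds that the envelope is opened in the call that books the visit: "The primary health care staff member opens the envelope during the phone call (but does not reveal the allocation to the participant". Randomisation also states: "All patients who give informed consent and who fulfil the eligibility criteria will be randomised".
- **First visit.** Recruitment procedures: "During the first visit to the PCRU, the participants sign a letter of informed consent before the treatment starts". Under Randomisation, the treating provider tells the patient the arm at this visit.
- **Baseline data.** Data collection: "Data will be collected at baseline (after randomisation and before the treatment starts". Baseline: "Baseline data will be collected during the first visit or at 1–4 days before the first visit at the PCRU".
- **Exclusion criterion.** Characteristics of participants lists "lack of written informed consent" among the exclusions.
- **Analysis.** Statistical analysis promises an "intention-to-treat (ITT) analysis for all participants that are included in the study". The primary analysis compares groups on the change in ODI from baseline to 6 months, by one-way ANOVA.

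**The concern.** Two separate weaknesses follow from the order of events.

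**Baseline measurement.** ODI is self-reported, and the primary analysis is a change from baseline. A patient who has just learned that the allocation is advice only, or the combined treatment, may rate current limitation differently from one who does not know. A shift of that kind in one arm goes straight into the difference in change. Blinding of outcome assessors and analysts, promised under Blinding, does not help, because the patient is the one answering. The planned adjusted regression does not list baseline ODI as a covariate, and adjusting for a baseline already affected by the arm would not cleanly remove the problem. The subgroup split at a baseline ODI of 40% rests on the same score.

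**Analysis set.** Between the opening of the envelope and the signature, a patient may fail to attend or decline to sign. The clinic already knows the arm by then. If such patients do not count as included, the analysed groups are no longer the groups that were randomised, and losses that differ by arm would not show in the ITT analysis.

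**Working it through.** The plan states no figure on this point, so the check is first one of sequence.

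**Step 1: order of events**

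| Step | Event | Section |
|---|---|---|
| 1 | Phone call: oral consent, eligibility check | Recruitment procedures |
| 2 | Same call: envelope opened, arm known to staff and withheld from the patient, visit booked | Randomisation |
| 3 | Questionnaire, if done 1–4 days before the visit | Baseline |
| 4 | First visit: written consent, examination, disclosure of the arm, and the questionnaire if not already done | Recruitment procedures; Study treatments; Randomisation; Baseline |
| 5 | Treatment starts | Data collection |

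The ordering rules for the questionnaire are that it follows randomisation and precedes treatment. Within step 4 its place relative to disclosure is not fixed. Step 3 comes before disclosure and is safe from this route; step 4 is not.

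**Step 2: effect on the primary contrast**

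Let a share f of one arm answer after disclosure and shift its reported baseline by s points on average, with no shift in the comparison arm. The mean reported baseline of that arm moves by f × s. Change is follow-up minus baseline, so mean change moves by the same amount in the opposite direction, and so does the difference between arms. If both arms shift, the bias is the difference of the two products, and equal shifts cancel.

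Both f and s are assumed. Bias in ODI points:

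| | s = 1 | s = 2 | s = 5 |
|---|---|---|---|
| f = 0.25 | 0.25 | 0.5 | 1.25 |
| f = 0.5 | 0.5 | 1 | 2.5 |
| f = 1 | 1 | 2 | 5 |

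The section Required sample size sets a target difference of 10 points. The range is therefore 0.25/10 = 2.5% to 5/10 = 50% of the target. A middle case, f = 0.5 and s = 2, gives 1 point, or 10%.

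**Step 3: the analysis set**

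- Under Characteristics of participants, a patient without written consent is excluded.
- Under Recruitment procedures, the signature is given at the first visit.
- Under Randomisation, the envelope was opened earlier, on the phone.
- This exclusion can therefore only be settled after randomisation.
- Under Statistical analysis, the ITT set is those included in the study. A patient who is randomised but never signs falls inside or outside it depending on how *included* is read.

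The documents give no loss rates between the call and the signature, so no size is attached to this part.

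**The case against.** **The phone-first design is deliberate.** Characteristics of participants says that inclusion mimics Swedish primary care, where first contact is usually by phone. That stands as a reason to screen and book by phone. It is no reason to leave the questionnaire unordered relative to disclosure, or the ITT set loosely worded.

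**Concealment is sound up to opening.** Sequentially numbered, opaque, sealed envelopes are opened only after the phone eligibility check. This stands: the weakness lies in what follows randomisation, not in predicting the next allocation.

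**Contamination is possible, not stated.** Staff withhold the arm on the phone, so those answering before the visit have not been told it. The schedule figure is not shown, and within-visit order may be fixed in a fuller document. This stands and limits the claim to patients who answer at the visit after disclosure. The sections at hand, however, give a rule for timing, and that rule permits the exposed order.

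**The outcome definition.** Primary outcome measure names the 6-month score. If the test were run on that score alone, the baseline route would not touch it. The Statistical analysis section, however, states the primary analysis as a change from baseline.

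**The word *included* may simply mean randomised.** Randomisation speaks of including subjects up to 600, and the Design section commits to the CONSORT extension for pragmatic trials. This is a fair reading, but it is not secured by the text.

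Three stronger readings are tempting and not supported:

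- A reader might infer that the protocol contradicts itself by randomising before consent. The Randomisation section speaks of informed consent without saying written, and the oral consent on the phone satisfies it.
- A reader might infer that the first-visit examination serves to remove randomised patients. The criterion concerns a *known* specific pathology, and nothing makes the examination a second eligibility screen.
- A reader might conclude that envelopes should be opened at the visit. The arm decides which provider, or both, must be booked, so this is not clearly a cheap change.

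**Conclusion.** The concern holds in limited form, as something that should be fixed rather than a fault that invalidates the trial. The text lets baseline ODI be answered with the arm known, for patients who complete the questionnaire at the first visit. It also lets a randomised patient be excluded for want of a signature, with an ITT definition that does not clearly retain that patient.

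The size of the first part is f × s, or 0.25 to 5 points over the assumed range. It rests on an unknown share answering after disclosure, on a shift that differs between arms, and on the primary test being run on change. The second part has no documented size. A reader might infer that patients will in fact be dropped or that baseline scores are in fact distorted; the documents say neither. They only fail to prevent it.

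**What to change.** 1. **Questionnaire before disclosure.** Require the online baseline questionnaire to be submitted before the patient learns the arm, either in the existing window of 1–4 days before the visit or on arrival, before meeting the provider. Add this to the Data collection and Baseline sections. Cost: one sentence and an instruction to the units.
2. **Analysis set.** Define the ITT set as all randomised patients, meaning all for whom an envelope was opened, subject to consent for use of their data. Report by arm how many did not attend and how many did not sign. Cost: wording, and a count kept at each unit.
3. **Consent before opening, where feasible.** Obtain written or electronic consent before the envelope is opened. Study information is already e-mailed, but under Recruitment procedures it goes out after the phone contact, so the opening would have to wait for the signed form. Cost: an added consent step and some delay in booking.

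Recruitment began on 1 April 2017, before protocol version 1 of 9 July 2017, so these are changes to a running trial and their date should be recorded. Recruitment procedures already provides for updating procedures across units. For patients enrolled before the change, if the system holds submission times, report how many baseline questionnaires were completed before the day of the visit.
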